**Table 10-1 Best Overall Response**

| Target lesions | Non-Target lesions | New Lesions | Overall response |
|----------------|--------------------|-------------|------------------|
| CR             | CR                 | No          | CR               |
| CR             | SD                 | No          | PR               |
| PR             | CR or SD           | No          | PR               |
| SD             | CR or SD           | No          | SD               |
| PD             | Any                | Yes or No   | PD               |
| Any            | PD                 | Yes or No   | PD               |
| Any            | Any                | Yes         | PD               |

Subjects with a global deterioration of health status requiring discontinuation of treatment without objective evidence of disease progression at that time should be classified as having

“symptomatic deterioration.” Every effort should be made to document the objective progression even after discontinuation of treatment.

In some circumstances, it may be difficult to distinguish residual disease from normal tissue. When the evaluation of complete response depends on this determination, it is recommended that the residual lesion be investigated (biopsy) to confirm the complete response status.

## 11 ADVERSE EVENTS AND SERIOUS ADVERSE EVENTS

### 11.1 Definition of Adverse Event (AE)

According to 21 CFR 312.32(a): “An adverse event is defined as any untoward medical occurrence associated with the use of a drug in humans, whether or not considered drug related.” An AE can therefore be any unfavorable and unintended sign (including an abnormal laboratory finding, for example), symptom, or disease temporally associated with the use of an investigational product, whether or not related to the investigational products. AEs may also include pre- or post-treatment complications that occur as a result of protocol specified procedures, lack of efficacy, overdose, drug abuse/misuse reports, or occupational exposure. Pre-existing events that increase in severity or change in nature during or as a consequence of participation in the clinical study will also be considered AEs. The subject’s baseline for purposes of assessing toxicity is established by the active medical conditions present directly prior to initiation of Course 1, Week 1 investigational product administration.

An AE does not include the following:

- Medical or surgical procedures such as surgery, endoscopy, tooth extraction, and transfusion. The condition that led to the procedure may be an adverse event and must be reported.
- Pre-existing diseases, conditions, or laboratory abnormalities present or detected before the infusion of investigational product that do not worsen.
- Situations where an untoward medical occurrence has not occurred (e.g., hospitalization for elective surgery, social and/or convenience admissions).
- Overdose without clinical sequelae.
- Any medical condition or clinically significant laboratory abnormality with an onset date before infusion of investigational product and not related to a protocol-associated procedure is not an AE. It is considered to be pre-existing and should be documented on the medical history CRF.
- Abnormal laboratory values or tests that are not clinically significant or do not require therapy.

A suspected adverse reaction is any AE for which there is a reasonable possibility that the investigational product caused the AE. For the purposes of IND safety reporting, “*reasonable possibility*” means there is evidence to suggest a causal relationship between the investigational product and the AE. *Suspected* adverse reaction implies a lesser degree of certainty about causality than adverse reaction, which means any AE caused by an investigational product.

Life-threatening AE or life-threatening suspected adverse reaction is an AE or suspected adverse reaction that, in the view of either the investigator or study Sponsor, places the study participant at immediate risk of death. It does not include an AE or suspected adverse reaction that, had it occurred in a more severe form, might have caused death.

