## 5.2 Dose-Limiting Toxicity (DLT)

A DLT is an event, defined below, which, in the opinion of the investigator, is possibly, probably, or definitely attributable to the CAR T cell product and which occurs from the time of initial CAR T cell infusion through 28 days following the final CAR T cell infusion. The Maximum Tolerated Dose Regimen (MTDR) will be established by the occurrence of DLTs which occur from the time of initial CAR T cell infusion through 7 days following the final CAR T cell infusion received during Course 2. See Section 9.9.4 Definition and determination of MTDR and RP2DR, for information on establishing MTDR.

The definition of a DLT includes all  $\geq$  Grade 3 Common Terminology for AEs (CTCAE) v5 toxicities **except**  $\geq$  Grade 3 toxicities that are known to be related to CAR T cells [45], listed below.

Exceptions to  $\geq$  Grade 3 DLTs:

- Grade 3 CRS that decreases to  $\leq$  Grade 2 within 72 hours of onset
- $\geq$  Grade 3 hypotension, fever, chills not controlled with medical intervention that decrease to  $\leq$  Grade 2 within 72 hours
- $\geq$  Grade 3 activated PTT, fibrinogen, and/or INR that are asymptomatic and resolve within 72 hours
- $\geq$  Grade 3 hypoglycemia and/or electrolyte imbalance that are asymptomatic and resolve within 72 hours
- $\geq$  Grade 3 nausea and/or vomiting that decrease to  $\leq$  Grade 2 within 7 days

- Arm A and B only: Grade 3 neurological adverse event that decreases to  $\leq$  Grade 2 within 7 days
- Arm C only: Grade 3 neurological adverse event that decreases to  $\leq$  Grade 2 within 21 days (treatment with dexamethasone and/or bevacizumab is allowed)

The definition of a DLT also includes any related toxicity lasting  $> 14$  days which prohibits the subject from meeting criteria for subsequent CAR T cell infusion.

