Within each Arm, the toxicities observed with each DR will be summarized in terms of type (organ affected or laboratory determination, such as ANC), severity (by NCI CTCAE v5), CRS grading, neurologic grading, and nadir or maximum values for the laboratory measures, date of onset, and attribution. Tables will be created to summarize these toxicities by Arm and DR with both number of subjects and number of incidences. The evaluation taking place within 2 days prior to initial CAR T cell infusion will serve as the baseline measurement.

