### 11.3.2 Relationship of adverse event to treatment

The investigator will assess the potential relationship of the AE to investigational product using the following descriptions.

- **Not Related:** This category applies to an AE that is clearly not related to the investigational agent/procedure, beyond a reasonable doubt. That is, another cause of the event is most plausible and/or a clinically plausible temporal sequence is inconsistent with the onset of the event and the exposure to study drug and/or a causal relationship is considered biologically implausible.
- **Unlikely Related:** This category applies to an AE that is doubtfully related to the investigational agent/procedure. That is, another cause of the event is highly likely and/or there is not a reasonable temporal sequence from administration of the study drug or one that follows a known or expected response pattern to the suspected study drug. The event could readily have been produced by a number of other factors.
- **Possibly Related:** This category applies to an AE that follows a reasonable temporal sequence from administration of the study drug and that follows a known or expected response pattern to the suspected study drug, but that could readily have been produced by a number of other factors.
- **Probably Related:** This category applies to an AE that is likely related to the investigational agent/procedure. That is, the AE has a temporal relationship to the administration of the investigational agent(s) or research intervention and follows a known or suspected pattern of response.
- **Definitely Related:** This category applies to an AE that is clearly related to the investigational agent/procedure. That is, the AE has a temporal relationship to the administration of the investigational agent(s) or research intervention and follows a known or suspected pattern of response.

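### Section 11.1 keeps laboratory abnormalities that need no therapy out of the AE record, while section 5.2 can count the same values as DLTs, so the DLT count may be understated

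*Protocol*

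**What the plan says.** Section 11.1 first allows that an AE can be a laboratory finding ("including an abnormal laboratory finding, for example"). It then lists what an AE does not include, and the last item is "Abnormal laboratory values or tests that are not clinically significant or do not require therapy". The two conditions are joined by an or, so either one is enough to exclude a value.

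Section 5.2 counts as a DLT an event that the investigator judges "possibly, probably, or definitely attributable to the CAR T cell product and which occurs from the time of initial CAR T cell infusion". It covers everything from "Grade 3 Common Terminology for AEs (CTCAE) v5 toxicities" upwards, apart from a list of exceptions. Two of these concern laboratory values: "Grade 3 activated PTT, fibrinogen, and/or INR that are asymptomatic and resolve within 72 hours", and "Grade 3 hypoglycemia and/or electrolyte imbalance that are asymptomatic and resolve within 72 hours". Each applies to that grade or higher and requires both absence of symptoms and resolution in time. Neither depends on treatment.

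Section 7.9 sets the capture period for AEs and section 11.3.1 their grading. Attribution is in section 11.3.2: "The investigator will assess the potential relationship of the AE to investigational product using the following descriptions". Section 9.2 asks for toxicity summaries, laboratory determinations included, with "nadir or maximum values for the laboratory measures, date of onset, and attribution".

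**The concern.** The two definitions can give opposite answers for one event. Because of the or, 11.1 removes even a clinically significant value if no therapy is needed. Under 5.2 the same value is a DLT if it is related, Grade 3 or higher and not excepted.

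A DLT needs a grade and an attribution, and the only procedures for assigning these are written for AEs. Whether such an event reaches the DLT count may then depend on whether therapy was thought necessary and not on its grade. Any error runs one way, towards fewer DLTs. DLTs drive the escalation rules (9.9.2), the MTDR (9.9.4) and the expansion halt (9.10). Under 8.1 a DLT also ends protocol therapy for that subject, so a missed one matters for the individual as well as for the count.

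**Working it through.** **1. The definitions side by side.** Take a related laboratory abnormality, new since the pre-infusion baseline, for which no therapy is needed.

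| Abnormality | AE under 11.1? | DLT under 5.2? | Other provision that would bring it to light |
|---|---|---|---|
| Grade 3+ electrolyte value, asymptomatic, resolved within 72 h | No | No | None needed; the sections agree |
| Grade 3+ electrolyte value, asymptomatic, longer than 72 h | No | Yes | Scheduled chemistry only |
| Grade 3+ ALT | No | Yes | Scheduled chemistry (7.12); not a re-infusion criterion |
| Grade 3+ neutrophil or lymphocyte value | No | Yes | Scheduled hematology (7.11); not a re-infusion criterion |
| Grade 3+ creatinine | No | Yes | Must be within the normal limit before each infusion (5.5.2) |
| Grade 3+ platelets | Normally yes, because 5.7.2 recommends transfusion | Yes | Platelet threshold in 5.5.2 |
| Grade 3+ fibrinogen, longer than 72 h | Normally yes, because 5.7.2 calls for replacement | Yes | Required only as a CRS laboratory test (7.13) |

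No sentence says that 11.1 gives way to 5.2. The real gap is mainly ALT, neutrophils and lymphocytes.

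**2. Which rules can be affected.**

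- Escalation (9.9.2): 1/3 calls for a second cohort, but read as 0/3 it escalates. 2/3 closes the DR, but read as 1/3 it continues.
- MTDR (9.9.4, cumulative rate below 34%): 3/6 = 50% fails; 2/6 = 33.3% passes.
- Expansion halt (9.10, rate above 33%): the printed limits reproduce, since 3/9, 4/12, 5/15, 6/18 and 7/21 are each 33.3% and every smaller denominator in each band gives a higher rate. A true 3/9 read as 2/9 = 22.2% would not halt.
- Grade 4 rule (9.9.3): an exact sequential binomial calculation over 24 subjects gives a suspension probability of 0.0077 at a true rate of 2.5% and 0.924 at 30%, against about 0.007 and 0.93 stated. The rule is confined to toxicities that needed medical intervention, so values needing no therapy are outside it by design and the conflict does not touch it.

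**3. Illustration of size, on assumed inputs.** The documents give neither the true DLT rate p nor the share f of DLTs lost through the AE exclusion. Suppose each DLT is lost independently with probability f, so that the observed rate is q = p(1 − f). With a higher DR available:

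- P(escalate) = (1 − q)³ + 3q(1 − q)⁵
- P(at most 2 DLTs in 6) is the binomial sum over 0, 1 and 2 with n = 6.

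For p = 0.40 and f = 0.20, q = 0.32 and P(escalate) = 0.68³ + 3 × 0.32 × 0.68⁵ = 0.314 + 0.140 = 0.454.

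| True p | f | q | P(escalate) | P(at most 2/6) |
|---|---|---|---|---|
| 0.30 | 0 | 0.30 | 0.494 | 0.744 |
| 0.30 | 0.10 | 0.27 | 0.557 | 0.798 |
| 0.30 | 0.20 | 0.24 | 0.622 | 0.846 |
| 0.30 | 0.30 | 0.21 | 0.687 | 0.888 |
| 0.40 | 0 | 0.40 | 0.309 | 0.544 |
| 0.40 | 0.10 | 0.36 | 0.378 | 0.627 |
| 0.40 | 0.20 | 0.32 | 0.454 | 0.706 |
| 0.40 | 0.30 | 0.28 | 0.536 | 0.780 |

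At f = 0 there is no bias. The table shows direction and sensitivity; it does not estimate what happens in this trial.

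**The case against.** Section 5.2 defines a DLT as an event in its own right and does not require it to be an AE first. Section 9.2 lists laboratory evaluations as safety data separately from AEs, and asks for laboratory toxicities to be summarized by severity and attribution. The weekly review in 9.11.1 names AEs and DLTs as separate items. Hematology and chemistry are drawn at every infusion visit. A careful team could therefore identify a laboratory DLT without an AE entry.

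This stands as mitigation, and it rules out several stronger readings that a reader might infer:

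- **That the DLT rate is understated.** This would follow only if sites screened for DLTs from AE entries alone, which the protocol does not say.
- **That every asymptomatic Grade 3 or higher laboratory value is a DLT.** Coagulation, hypoglycemia and electrolyte values that resolve within 72 hours are exempt.
- **That platelets, creatinine and fibrinogen are equally exposed.** Sections 5.5.2, 5.7.2 and 7.13 largely cover them.
- **That a frequency can be attached.** An assumed 5% to 10% of subjects with such an event would put at least one in 1 − 0.95³ = 14% to 1 − 0.90³ = 27% of cohorts of three. But the rate has no source in the documents, and having an event in a cohort is not the same as missing it.

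The mitigation does not remove the conflict. Section 9.2 calls for attribution but does not say how it is obtained for a laboratory value that is not an AE, and the only relationship scale is the one for AEs. Nor can 5.2 be read as silently limited to treated events: 9.9.3 states such a limit and 5.2 does not.

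**Conclusion.** The point holds as a conflict between two operative definitions. A related Grade 3 or higher laboratory abnormality that needs no therapy, and falls outside the 5.2 exceptions, is a DLT under 5.2 and not an AE under 11.1. No defined route leads to its being graded and attributed. The gap is mainly ALT, neutrophils and lymphocytes.

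The DLT count may therefore be understated for escalation, the MTDR and the expansion halt. The direction is certain if any event is lost, but whether any is lost, and how many, cannot be derived from the documents. With cohorts of three, a single event is enough to change a decision.

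**What to change.** Reconcile the two sections in one of two ways, or a combination:

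- State in 11.1 that the laboratory exclusion does not apply to any new or worsened abnormality of CTCAE v5 Grade 3 or higher, and that each is recorded, graded, attributed and assessed against 5.2 whether or not it is treated.
- If the sponsor does not intend some of these to be DLTs, say so in 5.2, so that both sections give the same answer. Which ones is the sponsor's clinical decision.

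Then check the laboratory data already collected for Grade 3 or higher values never assessed against 5.2. The version history dates the 11.1 exclusion to V5.1 (August 2021), after treatment had begun, so laboratory AE capture may also differ between earlier and later subjects in the pooled tables.

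The cost is a sentence, one review of existing data and some extra AE entries from tests already scheduled. The reported Grade 3 or higher rate may rise.

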## 11.2 Definition of Serious Adverse Event (SAE)

An AE or suspected adverse reaction is considered “serious” if, in the view of either the investigator or the study Sponsor, it results in any of the following outcomes:

- Death
- A life-threatening AE
- Inpatient hospitalization or prolongation of existing hospitalization
- Persistent or significant incapacity or substantial disruption of the ability to conduct normal life functions
- A congenital anomaly/birth defect
- A secondary malignancy

Important medical events that may not result in death, be immediately life-threatening, or require hospitalization may be considered serious when, based upon appropriate medical judgment, they may jeopardize the study participant and may require medical or surgical intervention to prevent one of the outcomes listed above.

## 11.3 Classification of an Adverse Event

### 11.3.1 Grading of adverse events

Wherever possible, all AEs will be graded using the NCI CTCAE v5, except grading of CRS which will be according to the CRS Grading Scale (Section 11.5 Cytokine Release Syndrome Grading). Individual neurologic symptoms should be graded using CTCAE v5, however cumulative neurologic toxicity will be graded according to the Neurologic Toxicity Grading System (Section 14, Appendix 4 – Neurologic Toxicity Grading System). The majority of AEs can be graded using these scales.

If an AE cannot be graded using the NCI CTCAE criteria, it should be graded as mild, moderate, severe, life-threatening, or death using the following definitions.

- **Mild (Grade 1):** Awareness of signs or symptoms, but easily tolerated and of a minor irritant type, causing no loss of time from normal activities. Symptoms do not require therapy or a medical evaluation. Signs and symptoms are transient.
- **Moderate (Grade 2):** Events that introduce a low level of inconvenience or concern to the participant and may interfere with daily activities but are usually improved by simple therapeutic measures. Moderate experiences may cause some interference with functioning.
- **Severe (Grade 3):** Events that interrupt the participant’s normal daily activities and generally require systemic drug therapy or other treatment. They are usually incapacitating.

- **Life-threatening (Grade 4):** Events that place the participant at immediate risk of death or are disabling.
- **Death (Grade 5):** Events that result in death.

To make sure there is no confusion or misunderstanding of the difference between the terms "serious" and "severe," which are not synonymous, the following note of clarification is provided. The term "*severe*" is often used to describe the intensity (severity) of a specific event (as in mild, moderate, or severe myocardial infarction); the event itself, however, may be of relatively minor medical significance (such as severe headache). This is not the same as "*serious*", which is based on participant/event outcome or action criteria usually associated with events that pose a threat to a subject's life or functioning. Seriousness (not severity) serves as a guide for defining regulatory reporting obligations.

### 11.3.2 Relationship of adverse event to treatment

The investigator will assess the potential relationship of the AE to investigational product using the following descriptions.

- **Not Related:** This category applies to an AE that is clearly not related to the investigational agent/procedure, beyond a reasonable doubt. That is, another cause of the event is most plausible and/or a clinically plausible temporal sequence is inconsistent with the onset of the event and the exposure to study drug and/or a causal relationship is considered biologically implausible.
- **Unlikely Related:** This category applies to an AE that is doubtfully related to the investigational agent/procedure. That is, another cause of the event is highly likely and/or there is not a reasonable temporal sequence from administration of the study drug or one that follows a known or expected response pattern to the suspected study drug. The event could readily have been produced by a number of other factors.
- **Possibly Related:** This category applies to an AE that follows a reasonable temporal sequence from administration of the study drug and that follows a known or expected response pattern to the suspected study drug, but that could readily have been produced by a number of other factors.
- **Probably Related:** This category applies to an AE that is likely related to the investigational agent/procedure. That is, the AE has a temporal relationship to the administration of the investigational agent(s) or research intervention and follows a known or suspected pattern of response.
- **Definitely Related:** This category applies to an AE that is clearly related to the investigational agent/procedure. That is, the AE has a temporal relationship to the administration of the investigational agent(s) or research intervention and follows a known or suspected pattern of response.

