### 9.9.3 Stopping rules

In the event of the following, further T cell infusions will be suspended pending review by the DSMB and consultation with the FDA:

- Death unrelated to disease progression or accidental trauma that occurs within 30 days of CAR T cell administration

To further protect the safety of patients, infusions will also be suspended pending review by the DSMB and consultation with the FDA if the lower bound of a 1-sided 80% exact binomial confidence interval of the discontinuation rate due to medically significant Grade 4 or greater events that are possibly, probably, or definitely attributable to CAR T cells is  $> 10\%$ .

Operationally, any of the following would trigger such a rule: 2 out of the first  $\leq 5$  subjects or 3 out of the first  $\leq 11$  patients or 4 out of the first  $\leq 18$  patients or 5 out of the first  $\leq 24$  have unacceptable toxicity or  $\geq$  Grade 4 AEs that are possible, probably, or definitely attributable to CAR T cells. If the true probability of  $\geq$  Grade 4 AE is 2.5%, the probability of study suspension under the above rule is approximately 0.007; if the true probability is 30%, the probability of suspension is approximately 0.93 (probabilities estimated from 5,000 simulations).

This rule will apply to medically significant (requiring medical intervention)  $\geq$  Grade 4 toxicities that are possibly, probably, or definitely attributable to CAR T cells, with the exception of Grade 4 CRS for  $< 72$  hours, and Grade 4 fever.

If this rule is met, further T cell infusions for all subjects enrolled will be immediately halted. A safety evaluation will be performed and reviewed with the FDA and DSMB prior to resuming any CAR T cell infusions.

Additionally, the Study Chair may shut down a DR at any time due to toxicities observed or efficacy observed at lower DRs.

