#### 11.4 Expectedness, Pre-Existing Conditions, and Persistent Adverse Events

- ***Expectedness:*** The study Sponsor will be responsible for determining whether an AE is expected or unexpected. An AE will be considered unexpected if the nature, severity, or frequency of the event is not consistent with the risk information previously described for the investigational product.
- ***Pre-Existing Conditions:*** If a pre-existing condition worsens in severity, the worsening may require reporting as an AE or SAE. In addition, if a condition present at baseline resolves and then recurs, the reoccurrence may require reporting as an AE or SAE.
- ***Persistent Adverse Events:*** A persistent AE is one that extends continuously, without resolution (is ongoing). A persistent AE is reported only once unless the grade and/or frequency become more severe. If the grade becomes more severe the original AE will be considered to have stopped on the date the severity increased and the AE must be reported again with the higher grade and/or frequency.

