### **11.9 On-Target, Off-Tumor Toxicities**

On-target off-tumor toxicities are toxicities attributable to the direct effect of CAR T cells on tissue (e.g. organ damage caused by CAR T cell direct targeting of organ cells) and not associated with a more global syndrome attributable to the CAR T cell (eg, CRS or pseudoprogression).

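### Section 11.3.2 makes a known or expected pattern a condition of Possibly Related, so a well-timed novel event with a competing cause can drop out of the DLT and suspension counts

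*Protocol*

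**What the plan says.** Section 11.3.2 tells the investigator to assess relationship to the investigational product using five descriptions. The ones that matter here are:

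- **Possibly Related**: the timing is reasonable "and that follows a known or expected response pattern to the suspected study drug", although other factors could also explain the event.
- **Unlikely Related**: another cause is highly likely, and/or there is no reasonable temporal sequence "or one that follows a known or expected response pattern to the suspected study drug".
- **Probably and Definitely Related**: there is a temporal relationship and the event "follows a known or suspected pattern of response".

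Three safety rules use the upper three categories as their entry condition:

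- Section 5.2 counts a DLT only if the event, in the investigator's opinion, "is possibly, probably, or definitely attributable to the CAR T cell product".
- Section 9.9.3 bases its suspension count on medically significant Grade 4 or greater events "that are possibly, probably, or definitely attributable to CAR T cells".
- Section 11.7 requires SAEs (and deaths) more than 30 days after the last infusion to be reported only if they fall in one of those three categories.

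Elsewhere the protocol applies no pattern test. Section 11.1 defines a suspected adverse reaction by a reasonable possibility of causation, meaning evidence that suggests a causal link. Section 6.4 provides for a new Grade 3 or higher toxicity, beyond those it lists, that is possibly, probably or definitely attributable and meets the DLT definition.

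**The concern.** A Phase 1 trial of a CNS-delivered cell product has to detect toxicities that nobody has yet described. For a first case the investigator often has only plausible timing and no way to rule out the tumour. Possibly Related is the category meant for that situation. If it requires a pattern that is already known or expected, a first case cannot enter it, and Unlikely is the category that remains.

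The primary safety count is at stake. DLTs drive escalation (9.9.2), the 34% limit that defines the MTDR (9.9.4) and the expansion-cohort halt (9.10). Section 5.2 already exempts listed transient toxicities known to be related to CAR T cells, so novel events are an important part of what the count has to find. An attribution rule that filters them out can only lower the observed rate.

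**Working it through.** **1. The categories compared, for an event with reasonable timing.**

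| Category | Pattern wording | Competing cause | Counted? |
|---|---|---|---|
| Unlikely | no known or expected pattern is one route in | said to be readily available | no |
| Possibly | known or expected pattern required | said to be readily available | yes |
| Probably, Definitely | known or suspected pattern required | event judged likely or clearly related | yes |

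Unlikely and Possibly describe competing factors in the same way. Once timing is reasonable and another cause is available but not highly likely, the pattern clause is what separates an uncounted event from a counted one. The scale is also out of order: the pattern wording is looser for Probably and Definitely than for Possibly.

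**2. Which events are caught.** All of these must hold: good timing, a new kind of event, a competing cause, and an investigator who cannot call it likely related on a suspected pattern. If the investigator can do so, the event is Probably and is counted.

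**3. The plan's own operating figures.** Section 9.9.3 gives bounds of 2 in the first 5 or fewer, 3 in 11, 4 in 18 and 5 in 24, with suspension probabilities of about 0.007 at a true rate of 2.5% and 0.93 at 30%. An exact recursion, checked after every subject to n = 24, carries the probability of x events forward as f(n, x) = f(n−1, x)(1−p) + f(n−1, x−1)p and removes any path that reaches a bound. It gives 0.0077 and 0.924, so the stated figures reproduce.

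**4. Effect of lost events on suspension (illustration).** Suppose a share s of related Grade 4+ events is coded unlikely. The share is an assumption; the protocol gives none. The counted rate is 0.30 × (1 − s).

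| s | Counted rate | P(suspend) |
|---|---|---|
| 0 | 0.30 | 0.924 |
| 0.10 | 0.27 | 0.871 |
| 0.25 | 0.225 | 0.746 |
| 0.50 | 0.15 | 0.416 |

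**5. Effect on escalation (illustration).** Under 9.9.2 a regimen is passed with 0/3, or with 1/3 followed by 0/3:

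P(pass) = (1−p)³ + 3p(1−p)² × (1−p)³

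- p = 0.40: 0.216 + 0.432 × 0.216 = 0.309
- p = 0.30: 0.343 + 0.441 × 0.343 = 0.494
- p = 0.20: 0.512 + 0.384 × 0.512 = 0.709

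A true rate of 40% is above the 34% limit in 9.9.4. Recorded as 30% (0.40 × 0.75, a quarter lost) or 20% (0.40 × 0.50, half lost), it lies below. The 40% is assumed, as are both shares. Steps 4 and 5 also assume that each lost event makes an affected subject look unaffected.

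**The case against.** The case on the other side limits the point considerably.

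- **A reader might infer that every new CAR T toxicity becomes Unlikely.** It does not. Probably and Definitely accept a suspected pattern, and Section 11.9 anticipates one: "On-target off-tumor toxicities are toxicities attributable to the direct effect of CAR T cells on tissue". A novel event that fits such a mechanism can still be counted.
- **A reader might take this to be the usual fate of a neurologic event in DIPG or DMG.** The protocol contradicts that. Section 6.2 names tumour inflammation-associated neurotoxicity, 6.4 describes neurologic changes after infusion, and 5.2 has neurologic exceptions by arm. Such events meet the known-or-expected test and can be Possibly Related even when tumour competes.
- **A reader might infer that an event can hardly be both related and unexpected.** Section 11.4 says otherwise: "An AE will be considered unexpected if the nature, severity, or frequency of the event is not consistent with the risk information previously described". An event of known type can be unexpected in severity or frequency alone, and 11.8 has its own causality test with no pattern clause.
- **Some category descriptions mention the procedure as well as the agent.** This does not support a downward bias. Merging catheter events into product attribution would raise the DLT count.
- **Section 5.2 rests on the investigator's opinion and does not cite 11.3.2, and the Unlikely sentence is badly built.** Both are true, so an investigator may well code sensibly. But 11.3.2 is where the protocol defines the terms and instructs the investigator to use them, and 6.4 shows that novel toxicities are meant to count. The wording should not work against that intention.
- **Other safeguards exist.** SAEs through day 30 are reported whatever their attribution. Death within 30 days not due to progression or accidental trauma suspends infusions without an attribution test. The Study Chair may close a regimen, safety is reviewed weekly, and the DSMB reviews toxicity. Section 7.19.1 gives late events a second route. These mean such events may be seen, but they do not put an ambiguous, non-fatal novel event into the DLT count.

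**Conclusion.** The point holds in a limited form. As written, Possibly Related is stricter on pattern than the two categories above it and out of line with 11.1 and 6.4. Followed literally, it leaves a well-timed novel event with a competing cause out of the DLT count, the Grade 4+ suspension count and related-only SAE reporting after day 30, unless the investigator can call it likely related. The direction of bias in the observed DLT rate is down.

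The size is unknown. Nothing in the protocol gives the share of events affected or shows that any event has been coded this way, and described neurologic patterns fall outside the gap. A rise in the chance of passing a regimen from 0.31 to 0.49 or 0.71 shows what a loss of a quarter or a half would do at an assumed 40% true rate. It is not an estimate for this trial. The suspension figures need the same caution, and more so for deaths, since deaths within 30 days not due to progression or accidental trauma have their own trigger. This should be fixed, but it does not show that the safety counts have failed.

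**What to change.** Amend Section 11.3.2 as follows:

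- Define Possibly Related as a reasonable temporal sequence in which a causal role of the product cannot be excluded, even if other factors could have produced the event.
- Remove the pattern condition from both Possibly and Unlikely.
- Treat a known or suspected pattern as supporting evidence only for Probably and Definitely, not as a requirement.
- State that these categories follow the reasonable-possibility standard in Section 11.1.

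As a precaution, re-review Grade 3 or higher events already coded unlikely against the revised wording.

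The cost is a protocol wording change and a one-time review. The observed DLT rate may come out slightly higher.
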